### 2.7. Interventions

#### 2.7.1. Administration of the App

Participants will be instructed to use the App autonomously for 4 weeks at home, in addition to their usual treatment, during the period of using the App (T1 for fAPP group, T2 for dAPP group). According to their assigned group, each participant will receive basic instructions from the researcher on how to use the App.

As the purpose of using the App is to obtain an additional stress relief effect in the usual treatment for patients with depression, the schedule for the App will not be strictly controlled; the researchers will provide a 4-week schedule as a guideline to ensure the use of more than the minimal. As a minimum standard for usage, the schedule will guide participants to use the components of each module at least once a day, 6 days a week or more, and the use of additional content is left to the participant’s discretion. However, regarding the meditation module, the participants will be guided to conduct training after completing psychoeducation in consideration of the characteristics of the content. The App has implemented a system that alerts the user twice per day at a time they select if it is not utilized at least once per day. The researcher will help participants who have provided permission to activate the alarm system in the App. However, whether a participant follows these guidelines is not a determining factor in excluding respective participants’ data.

#### 2.7.2. Usual treatment for depression

All participating patients will continue all of their usual treatments for depression during the research period. To minimize the confounding effect of medication, the use of new psychiatric medications, including antidepressants and benzodiazepines, will be limited. The use of zolpidem and zopiclone for insomnia is possible. To participate in the study, a stable dosing period of 4 weeks is required, so considering the course of psychiatric drug treatment, in general, the possibility of changing medication will not be high. However, psychiatrists will address any changes in depression symptoms of participants immediately after they are identified. Should there be medication changes, participants’ will be entitled to withdraw from the study, and our research team will assess their situation to see if they need another treatment.

### 2.8. Assessments and outcomes

Assessments will be obtained through the clinician rating scale and self-rating scales during hospital visits. Table 2 presents the schedule for assessments. Assessments conducted at the hospital visits were acquired at the baseline (V_0_) and every 2 weeks (V_1_, V_2_, V3, and V4) during T1 and T2. The baseline assessments will be collected when participants are enrolled and will include their sociodemographic and clinical characteristics. All instruments have been translated to Korean with reliable psychometric properties. The data collection process implanted in the objective monitoring module of the mobile App will be activated through an ID issued after enrollment and randomization.

**TABLE 2 T2:** Schedule for assessments.

Assessments	Baseline	Visit			
		**V1**	**V2**	**V3**	**V4**
Mini international neuropsychiatric interview	V				
Depression, anxiety, and tress scale	V	V	V	V	V
Perceived stress scale	V		V		V
Posttraumatic embitterment disorder scale	V		V		V
Nine-item patient health questionnaire	V	V	V	V	V
Hamilton depression rating scale	V	V	V	V	V
Intervention engagement					V

### 2.9. Diagnostic interview

The Mini International Neuropsychiatric Interview (MINI) is a brief, organized diagnostic interview used to make psychiatric diagnoses using the DSM-IV and ICD-10 codes. The MINI was developed as a brief yet reliable structured psychiatric interview for multicentric clinical trials and epidemiology investigations (47).

### 2.10. Primary outcome measures

#### 2.10.1. Depression, anxiety, and stress scale (DASS-21)

The DASS-21 is s a self-report measure of anxiety, depression, and stress, developed by Lovibond for use in varied situations (48). Eun-Hyun Lee developed the Korean version of DASS-21 in 2018 (49). This version was evaluated in Korean-speaking samples and demonstrated that the items had been translated and adapted adequately and appropriately. The Korean version of DASS-21 was assessed on 481 Korean adults, and the Cronbach’s α was 0.93.

### 2.11. Secondary outcome measures

#### 2.11.1. Perceived stress scale (PSS)

The perceived stress scale (PSS) is designed to assess the respondents’ perception of their stress as unpredictable, uncontrollable, and overwhelming (50). The current study will utilize the validated Korean version of the PSS, which is a 10-item self-report questionnaire using a five-point Likert scale ranging from 0 (never) to 4 (very often). Total scores range from 0 to 40, with higher scores indicating increased perceived stress (Cronbach’s α = 0.819) (51).

#### 2.11.2. Posttraumatic embitterment disorders scale (PTED)

Posttraumatic Embitterment Disorder Self-Rating Scale (PTED Scale) was developed to evaluate the characteristics of embitterment reactions to negative life events (52). The PTED Scale, that consists of 19 items, asked participants to score their reactions to each negative life event that occurred in the recent years using a five-point scale ranging from 0 (not true at all) to 4 (extremely true). The PTED Scale was translated and validated in Korean with high internal consistency (Cronbach’s α = 0.962) (53).

#### 2.11.3. Nine-item patient health questionnaire (PHQ-9)

The Patient Health Questionnaire (PHQ-9) is a nine-item version of the historical Primary Care Evaluation of Mental Disorders (PRIME-MD), that was shortened to maximize clinical usefulness (54). The total score can range from 0 to 27, and each item is rated on a scale of 0–3. Mild, moderate, and severe depression severity levels are represented by the total scores of ≥ 5, ≥ 10, and ≥ 15, respectively (55). The PHQ-9 was translated and verified in Korean with strong internal consistency (Cronbach’s α = 0.86) (56).

#### 2.11.4. Hamilton depression rating scale (HAM-D)

The Hamilton Depression Rating Scale (HAM-D) is an inventory of questions used to detect and assess the severity of the signs and symptoms of depression in individuals who have been diagnosed with clinical depression (57). The 17-item version of the HAM-D is more widely used than the 21-item version, that includes four extra items that assess symptoms related to depression, such as paranoia and obsession, rather than the severity of the depressive symptoms. The HAM-D was translated and validated in Korean with good internal consistency (Cronbach’s α = 0.76) (58).

#### 2.11.5. Intervention engagement

Track and change functionalities (log files) will be used to evaluate activities on the app, such as the number of visits, duration between logins, and the number of usages of each category. Usage data on the App online server will also provide information on how patients utilize online modules (frequency, length, order, completion), how they rank them, and how they adhere to them. All patient data from the server will be secured using Hypertext Transfer Protocol Secure, ensuring that no third parties may see it while it is being transferred. Only the research assistants will be allowed to request and evaluate patient data since data access from the server is additionally authorized through a pass provided by the study coordinator.

### 2.12. Sample size and power calculations

To the best of our knowledge, there are no studies on stress-reduction programs for depression patients using a mobile application; hence, we have assumed the sample size based on the effect size of 0.28, being half of the effect size of 0.56 reported in a previous study that applied MBSR in patients with depression (59). For all patients with depression, the change in DASS-21 score from pre- to post-administration of the App would be analyzed using analysis of variance for a 2 × 2 crossover design (60). As we have assumed no carry-over effects, this was not considered in calculating the sample size. Sample size calculations were conducted using the statistical software G * Power 3.1.9.2 (61). The minimum sample was identified as 172 (fAPP = 86, dAPP = 86) based on an estimated between-group effect on post-intervention stress outcomes between the fAPP and dAPP with a power of 0.95 and an alpha of 0.05. Therefore, the current study will enroll 215 participants and allow for up to a 20% loss to follow-up, expecting a minimum effective sample size of 172 individuals.

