### 2.13. Data analyses

Data analysis will adhere to CONSORT rules (62), i.e., primarily on an intention-to-treat basis. The pre-randomization scores in the two conditions prior to receiving the intervention will be compared to ensure absence of significant differences between them on the outcome measures. Then, a multilevel linear mixed model will be computed, successfully managing missing data. The first evaluation of participants with missing data will assume that data are missing at random in the linear mixed model. Multiple imputation, last observation carried forward imputation, and assessment of the per protocol completers will be used to assess the sensitivity of this assumption, which should minimize the number of missing data. All measurement items will be incorporated into the model. The parameters will be estimated using a restricted maximum likelihood approach. If baseline differences are found, they will be included as variables in the linear mixed model. All analyses will be performed with SPSS v26.0.

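### The power paragraph attaches 95% power at effect size 0.28 to a between-group post-treatment comparison that has about 45%; the 95% holds only for a crossover contrast under conditions the paragraph does not state

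*Protocol article*

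**What the plan says.** All the sizing information is in section 2.12 of the protocol article.

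- **Effect size:** "the effect size of 0.28, being half of the effect size of 0.56 reported in a previous study that applied MBSR" in patients with depression. The paragraph does not say whether 0.28 is a between-patient d, a within-patient dz or Cohen's f.
- **Analysis:** the pre-to-post change in DASS-21 "would be analyzed using analysis of variance for a 2 × 2 crossover design".
- **Carry-over:** "As we have assumed no carry-over effects, this was not considered in calculating the sample size".
- **Comparison that the number rests on:** "an estimated between-group effect on post-intervention stress outcomes between the fAPP and dAPP with a power of 0.95" and an alpha of 0.05, sidedness not given. The resulting minimum is 172, 86 per group.
- **Attrition:** 20% loss to follow-up, hence 215 enrolled.

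Section 2.1 confirms that the trial is a crossover with two 28-day periods and no wash-out. Section 2.13 says that "a multilevel linear mixed model will be computed".

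**The concern.** The paragraph describes two different contrasts and gives one power for both. A between-group comparison of post-intervention scores uses each patient once and carries the full between-patient variance. A crossover contrast uses each patient as their own control, so its power depends on the within-patient correlation and on the absence of carry-over. The same 0.28 and the same 172 give very different power under the two.

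The between-group wording also matches the primary hypothesis at the end of the Introduction: four weeks of the App plus usual care against usual care alone. A reader will therefore take the trial to be almost certain to detect a deliberately conservative effect in that comparison. If its power is nearer one half, a null result there would be misread as evidence that the App does not work.

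**Working it through.** **Inputs.** Effect 0.28 (half of 0.56), 86 per group, 172 in total, alpha 0.05, target power 0.95, 20% loss: all from section 2.12. Assumed: two-sided alpha; within-patient correlation ρ between 0 and 0.7; SD of 1 at each visit. Power is from the noncentral t distribution.

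**1. Attrition.** 172 / (1 − 0.20) = 215. This reproduces.

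**2. The plan's power, crossover on post scores.** Noncentrality = dz × √N, df = N − 2.
- dz = 0.28, N = 172: 0.28 × √172 = 3.672, df 170, power **0.955**.
- The smallest even N reaching 0.95 is 168 (power 0.950).

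The stated power is therefore reproduced on this reading, to within four patients.

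**3. The comparison as worded, two groups on post scores.** Noncentrality = d × √(n/2), df = 2n − 2.
- d = 0.28, n = 86: 0.28 × √43 = 1.836, power **0.447** (0.573 if one-sided).
- Power 0.95 at d = 0.28 needs 333 per group, 666 in total.
- With 86 per group, power is 0.80 at d = 0.43 and 0.95 at d = 0.553. At d = 0.56 it is 0.955.

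With the baseline (V0) score as covariate at correlation r, d is replaced by d / √(1 − r²):

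| r (assumed) | 0.28 / √(1 − r²) | Power, 86 per group | d for 80% power |
|---|---|---|---|
| 0.5 | 0.323 | 0.56 | 0.37 |
| 0.6 | 0.350 | 0.63 | 0.34 |
| 0.7 | 0.392 | 0.72 | 0.31 |

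**4. Crossover on post scores, 0.28 as a between-patient d.** dz = 0.28 / √(2(1 − ρ)), N = 172, no carry-over:

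| ρ (assumed) | dz | Power |
|---|---|---|
| 0 | 0.198 | 0.73 |
| 0.3 | 0.237 | 0.87 |
| 0.4 | 0.256 | 0.92 |
| 0.5 | 0.280 | 0.955 |
| 0.6 | 0.313 | 0.98 |
| 0.7 | 0.361 | 0.997 |

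**5. Carry-over.** If a fraction λ of the effect persists into T2 for the App-first group, the crossover contrast estimates (1 − λ/2) times the effect. At ρ = 0.5:
- λ = 0.5: dz = 0.75 × 0.28 = 0.21, noncentrality 2.754, power **0.78**.
- λ = 1: dz = 0.5 × 0.28 = 0.14, noncentrality 1.836, power **0.45**.

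**6. Crossover on change scores, the outcome the paragraph names.** Take each period's change from its own start: V2 − V0 and V4 − V2. Their difference is 2·V2 − V0 − V4, with variance 6 − 6ρ under equal correlation, which is 3 at ρ = 0.5.
- Effect persists after T1: the contrast is 1 × 0.28, dz = 0.28/√3 = 0.162, noncentrality 2.120, power **0.56**.
- Effect vanishes after T1: the contrast is 1.5 × 0.28, dz = 0.42/√3 = 0.242, noncentrality 3.180, power **0.89**.

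Neither reaches 0.95 at this correlation.

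**The case against.** The strongest reply is that the trial is a crossover, the paragraph names a crossover ANOVA and says carry-over was left out, and on that analysis the halved effect does give 0.955 at 172. The between-group sentence is then loose wording. If 0.28 is a between-patient d, a correlation of 0.5 is a floor rather than a special value, and power only rises above it. Much of this stands. It would be wrong to say that the design as a whole has 45% power: that figure belongs to a comparison that ignores every T2 observation.

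A reader might also infer that the un-halved 0.56 was used, or that 0.28 was entered as Cohen's f, because 86 per group gives 0.955 at d = 0.56. The document does not support that. A parallel comparison at d = 0.56 and a crossover at dz = 0.28 have the same noncentrality (0.56 × √43 = 0.28 × √172 = 3.672) and the same minimum of 168, so the number cannot tell them apart.

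Two further inferences also fail. The gap between 168 and 172 is harmless, since 172 meets the target. The mixed model in section 2.13 is a standard analysis for a crossover and does not contradict sizing on an ANOVA.

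An article may leave software settings to a fuller document. What does not fall under that allowance is that the effect size, comparison and power it does print disagree.

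**Conclusion.** The point holds as a mismatch within section 2.12. For the between-group post-intervention comparison to which the paragraph attaches its 0.95, power at d = 0.28 is about 0.45 unadjusted and about 0.56 to 0.72 with baseline as covariate. Unadjusted, 95% needs d of about 0.55.

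The 0.95 is correct only for a crossover analysis of post scores with zero carry-over, where 0.28 is a dz or a between-patient d with correlation of at least 0.5. Below that correlation, power falls as far as 0.73 at zero correlation. At correlation 0.5, carry-over takes it to 0.78 (half the effect) or 0.45 (all of it). On change scores at correlation 0.5 it is 0.56 to 0.89.

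These figures assume two-sided alpha, equal variances and equal correlations; the correlations are assumptions, since the document gives none. Which input produced 172 cannot be established from the text.

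**What to change.** Rewrite the power paragraph so that effect size, comparison and power refer to one contrast. Either:

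- **(a) Between-group comparison at the end of T1.** State that 172 evaluable participants give 95% power for d of about 0.55, 80% for d = 0.43 and about 45% for d = 0.28, two-sided 0.05. Add that with V0 as covariate, at an assumed correlation of 0.5 to 0.7, power at 0.28 is about 0.56 to 0.72.
- **(b) Crossover contrast.** Remove the between-group post-intervention wording. Define 0.28 as dz, or give the assumed within-patient correlation. Say whether post scores or change scores are analysed, and recompute if change scores are meant. State two-sided alpha and that 95% holds only with zero carry-over, and give the power for lower correlation or partial carry-over.

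The cost is one paragraph. Neither option needs more participants, and the 172 and 215 can stand. The price is a power statement that is lower under (a) or openly conditional under (b).

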### 2.13. Data analyses

Data analysis will adhere to CONSORT rules (62), i.e., primarily on an intention-to-treat basis. The pre-randomization scores in the two conditions prior to receiving the intervention will be compared to ensure absence of significant differences between them on the outcome measures. Then, a multilevel linear mixed model will be computed, successfully managing missing data. The first evaluation of participants with missing data will assume that data are missing at random in the linear mixed model. Multiple imputation, last observation carried forward imputation, and assessment of the per protocol completers will be used to assess the sensitivity of this assumption, which should minimize the number of missing data. All measurement items will be incorporated into the model. The parameters will be estimated using a restricted maximum likelihood approach. If baseline differences are found, they will be included as variables in the linear mixed model. All analyses will be performed with SPSS v26.0.

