## 2. Materials and methods

### 2.1. Design

This study is a single blind, multicenter, randomized, controlled crossover trial (Figure 1). All subjects who meet the inclusion and exclusion criteria will be randomly assigned to the App first group (fAPP) or the wait list crossover group (dAPP). Due to the intervention’s nature, this will be a single-blind study in which the results will be assessed blindly but participants will be aware of their group assignment. Participants assigned to fAPP group will use the App initially for 28 consecutive days (T1). During T1, participants assigned to the dAPP group will maintain their usual treatment. After T1, for the next 28 consecutive days (T2), dAPP will use the App and fAPP will maintain the usual treatment, without a wash-out period. We assume that there would be no carry-over effect as the App utilized in this study is not a curative treatment but rather a tool for relieving stress. Therefore, we have decided to use a cross-over design without a wash-out period. Recommendation for Interventional Trials (SPIRIT) flow diagram is presented in Figure 2.

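### The three analyses named to check the missing-at-random assumption explore no plausible graded departure from it, and unrestricted LOCF shrinks the crossover contrast by 0 to 20% even when the assumption is true

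*Protocol article*

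**What the plan says.** Section 2.13 of the protocol article commits to intention-to-treat. Its primary analysis will "assume that data are missing at random in the linear mixed model", and of that model it says: "The parameters will be estimated using a restricted maximum likelihood approach". It then gives three further analyses an explicit job: "Multiple imputation, last observation carried forward imputation, and assessment of the per protocol completers will be used to assess the sensitivity of this assumption". The same sentence expects these methods to keep missing data to a minimum, which no analysis can do. No delta adjustment, pattern-mixture, reference-based or selection model is named, and LOCF is not confined to the treatment period in which the last score was taken.

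Three other sections bear on this:
- Section 2.1: after the first 28 days, "dAPP will use the App and fAPP will maintain the usual treatment, without a wash-out period".
- Section 2.8: assessments at baseline and "every 2 weeks (V_1_, V_2_, V3, and V4) during T1 and T2". V1 and V2 therefore fall in the first period, V3 and V4 in the second.
- Section 2.12: the trial will "enroll 215 participants and allow for up to a 20% loss to follow-up".

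Section 2.14 adds that the data of a patient who withdraws are left out of the analysis.

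**The concern.** A sensitivity analysis for MAR should ask how far the unseen scores would have to depart from what the model predicts before the conclusion changes. None of the three does so in a graded way.

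- **Multiple imputation**, as normally run, fills in scores under MAR. It largely repeats the mixed model.
- **Completers** are an unbiased sample only under a stronger assumption than MAR, and they are selected on behaviour after randomisation.
- **LOCF** assumes no change after the last score. In a crossover it can also use a score from one condition to represent the other.

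Outcome-related loss is plausible here. Participants know their allocation (2.1), the primary outcome is self-reported (2.10), a medication change entitles a participant to withdraw (2.7.2), and a clinical change involving risk implies removal from the project (2.15). A participant who worsens may leave before the worse score is recorded. The trial could then report a result as robust to missing data on analyses that could not have shown otherwise.

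**Working it through.** **The plan's own figure.** 172 / (1 − 0.20) = 215 enrolled, so the planned loss is up to 0.20 × 215 = 43 participants. This reproduces section 2.12. The plan gives no figure for the sensitivity analyses.

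**Estimator used for the check.** With end-of-period scores, the App benefit is

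E = ½ [mean(V4 − V2) in fAPP − mean(V4 − V2) in dAPP].

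This is a simplification of the planned mixed model.

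**LOCF.** The last visit attended decides what happens:

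| Last visit | V4 under LOCF | V2-V4 contrast |
|---|---|---|
| V2 or V1 | score from the other condition | exactly 0 |
| Baseline | pre-treatment score | exactly 0 |
| V3 | score from the same period | not forced to 0 |

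Let q be the share last seen at V2 or earlier, equal in both sequences and unrelated to outcome. Each mean change is multiplied by (1 − q), so E under LOCF = (1 − q) × E.
- All loss after V3: q = 0, shrinkage 0%.
- Half the 20% by V2: q = 0.10, shrinkage 10%.
- All 20% by V2: q = 0.20, shrinkage 20%.

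The article does not say when loss is expected, so the range is 0 to 20%.

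**Simulation.** Assumptions: 108 per sequence; within-person correlation 0.6; true benefit 0.28 × √(2 × (1 − 0.6)) = 0.250 SD; about 20% loss, all between V2 and V4 (the worst timing for LOCF); usual-care improvement of 0 or 0.2 SD per period; 1000 replicates. Multiple imputation is represented by its limit, regression imputation under MAR. Mean estimated benefit in SD:

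| Missingness | Multiple imputation | Completers | LOCF |
|---|---|---|---|
| Completely at random | 0.252 to 0.254 | 0.251 to 0.254 | 0.201 to 0.203 |
| MAR (depends on V2) | 0.250 to 0.251 | 0.243 to 0.246 | 0.191 to 0.197 |
| Not at random (dAPP users with worse unseen V4 leave) | 0.290 to 0.302 | 0.279 to 0.285 | 0.228 to 0.235 |

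When MAR fails, multiple imputation and completers are both too high, by about 12% (0.279 / 0.250) to 21% (0.302 / 0.250), and lie close together. When MAR holds, LOCF still differs from them by roughly a fifth. It falls slightly further in the MAR row because loss depends on V2, so the simple (1 − q) factor is no longer exact.

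**Size of an unexplored departure.** Suppose 20% of App-period scores are missing and truly δ SD worse than imputed, with usual-care scores imputed correctly.
- Loss in one sequence's App period only: ½ × 0.20 × δ = 0.1δ.
- Loss in both sequences' App periods, or a first-period between-arm contrast: 0.2δ.

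| δ (SD) | Overstatement (SD) |
|---|---|
| 0.5 | 0.05 to 0.10 |
| 1.0 | 0.10 to 0.20 |
| 1.5 | 0.15 to 0.30 |

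**Why this is not set against 0.28.** The planned figure is an "effect size of 0.28, being half of the effect size of 0.56" whose scale is not stated. At power 0.95 and two-sided alpha 0.05, reading it as a within-person dz or as Cohen's f gives 168 in total, near the stated 172. Reading it as a between-group d gives 333 per arm. It cannot be assumed to be in outcome-SD units.

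**The case against.** The strongest defence is that these are secondary analyses in a condensed article, that the primary mixed model is sound, and that imputation details and tipping points commonly sit in an analysis plan. This holds for detail. It does not cover a stated method with a stated purpose that it cannot serve.

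A second objection is that LOCF does depart from MAR: where scores improve over time, freezing a dropout at the last score is worse than MAR predicts. That is correct. A reader might infer that nothing in the plan lets dropouts do worse than predicted, or that all three analyses would agree while the result was wrong. The documents and the simulation do not support either inference. Under the not-at-random scenario LOCF visibly disagreed with the other two. The defect is that its departure is fixed and implausible, and that it disagrees just as readily when MAR is true.

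Third, it is an assumption that participants not helped by the App will leave. The article gives no expected reasons for loss, and section 2.4 pays for visits and rewards completing the App period.

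**Conclusion.** The point stands as a design weakness in the sensitivity analyses, not in the primary model. The named set explores no plausible graded departure from MAR, and neither agreement nor disagreement among its members is informative about MAR.

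LOCF shrinks the crossover effect by 0 to 20% for loss unrelated to outcome. The 20% is the worst case, in which all planned loss occurs by V2. The 0.1δ to 0.2δ overstatement is an illustration: its upper end needs 20% of App-period scores missing in both sequences, or a first-period contrast, with no offsetting error under usual care. The simulated figures also rest on the assumed correlation and dropout model.

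Three stronger readings should not be drawn:
- LOCF does not carry a V3 score across the switch, since V3 and V4 lie in the same period.
- The complaint is not that these analyses fail to test MAR. No analysis of observed data can, and section 2.13 promises only to assess sensitivity.
- A tipping value obtained by dividing 0.28 by 0.20 has no secure meaning while the scale of 0.28 is unstated.

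**What to change.** In section 2.13:
1. Replace LOCF as a check of MAR with delta-adjusted multiple imputation. Worsen the imputed App-period scores in both sequences over a range fixed in advance, for example 0 to 1.5 SD, and report the tipping point at which the conclusion changes. If LOCF is kept, confine it within a treatment period.
2. Optionally add reference-based imputation of App-arm dropouts from the wait-list arm. It applies to the first period only, so it cannot replace item 1 for dAPP participants lost while using the App in the second.
3. Label the per-protocol completers analysis as supplementary, not as a check of MAR.

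In section 2.14, reconcile the exclusion of withdrawn patients' data with intention-to-treat, so that scores collected before withdrawal enter the analyses unless the patient asks for removal. Otherwise none of these methods covers those who withdraw.

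The cost is a little extra analysis code: a constant added to imputed values for item 1, somewhat more programming for item 2. No further data collection is needed. The robustness statement may turn out less favourable.

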### 2.6. Randomization

Eligible volunteers will be randomly assigned to the fAPP or dAPP groups. Randomization is conducted using block randomization by each clinical center. To prevent bias toward one treatment group, eight patients will be configured in blocks and will be randomly assigned to the fAPP and dAPP groups within each block. For consistent allocation, randomization will be done using a pre-built program. This program is created by Korea University Guro Hospital to blind the researcher from assignment information in advance. The allocation sequence was prepared by researchers who did not participate in this protocol, and was used in the pre-built program. Researchers at each institution can conceal the sequence through the issued ID and password, and the process remains in a log.

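### A comparison of baseline scores decides which covariates enter the mixed model; the V0 score and centre should be fixed terms whatever the observed balance

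*Protocol article*

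**What the plan says.** Section 2.13 of the protocol article sets out a sequence. First, baseline scores in the two groups "will be compared to ensure absence of significant differences between them on the outcome measures". Next, "a multilevel linear mixed model will be computed", estimated by restricted maximum likelihood. Then comes the covariate rule: "If baseline differences are found, they will be included as variables in the linear mixed model". No level is given for the baseline comparison, and no covariate is fixed in advance.

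Three other statements bear on the point:

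- Section 2.6: "Randomization is conducted using block randomization by each clinical center". Three hospitals take part (section 2.4). Section 2.13 does not mention centre.
- Section 2.8: hospital assessments are "acquired at the baseline (V_0_) and every 2 weeks". Table 2 shows five outcome scales measured at baseline (DASS-21, PSS, PTED, PHQ-9, HAM-D).
- Section 2.13 also says "All measurement items will be incorporated into the model", which may mean that V0 is already one of the repeated responses.

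**The concern.** This is a stated rule, not a detail left for later; an analysis plan that followed it would inherit it. Allocation is random and concealed, so a baseline comparison tests a null hypothesis known to be true. A significant result marks a chance imbalance. It says nothing about whether the variable is prognostic, which is the reason to adjust.

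Two things are at stake. The primary model is not known until the baseline data have been inspected, and with five scales several models are possible. Precision may also be lost: the participant's own V0 score is usually the strongest predictor of the later score, yet under this rule it becomes a covariate only by accident. If V0 is already a response in the model, a triggered rule would put it in twice, as response and as covariate. That is a further reason to settle its role once.

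**Working it through.** **Inputs.** Section 2.12 gives "effect size of 0.28, being half of the effect size of 0.56", "with a power of 0.95 and an alpha of 0.05", 86 per group and 20% loss. Not in the document, so assumed: a two-sided test, a 0.05 level for the baseline comparison, and the V0-outcome correlation r (0.5 to 0.7).

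**1. The plan's own sample size.** The article does not say what kind of effect size 0.28 is. A two-sided paired t test with standardised mean difference 0.28 needs 168 in total; so does a two-group ANOVA with f = 0.28, that is d = 0.56. Both are within 3% of the stated 172, where power is 0.955. A two-sample t test with d = 0.28 needs 666 in total and does not reproduce it. Inflation: 172/(1 - 0.20) = 215, as stated. Both d = 0.28 and d = 0.56 are carried below.

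**2. How often the rule fires.** For one scale, 5% by construction. For at least one of five: 1 - 0.95^5 = 0.226 if the scales are independent, and about 0.15 if they correlate at 0.7.

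**3. Variance of the between-group contrast**, relative to an unadjusted end score:

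- adjusted for V0: 1 - r², a fall of 25% at r = 0.5 and 49% at r = 0.7;
- change score: 2(1 - r);
- adjusted against change: (1 - r²)/[2(1 - r)] = (1 + r)/2, a fall of 25%, 20% and 15% at r = 0.5, 0.6 and 0.7.

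**4. Power**, noncentral t with 86 per group. The noncentrality is d√(86/2) = 6.557d unadjusted, divided by √(1 - r²) when V0 is adjusted for. For d = 0.28 it is 1.836 unadjusted, 2.120 at r = 0.5 and 2.571 at r = 0.7.

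| d | r | End score, unadjusted | Change score | Always V0 |
|---|---|---|---|---|
| 0.28 | 0.5 | 0.447 | 0.447 | 0.559 |
| 0.28 | 0.6 | 0.447 | 0.532 | 0.626 |
| 0.28 | 0.7 | 0.447 | 0.654 | 0.725 |
| 0.56 | 0.5 | 0.955 | 0.955 | 0.988 |
| 0.56 | 0.6 | 0.955 | 0.983 | 0.995 |
| 0.56 | 0.7 | 0.955 | 0.997 | 0.999 |

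**5. The conditional rule itself**, simulated on the end score (6,000 trials per setting, no centre effect):

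| d | r | Unadjusted | Test, then adjust | Always V0 |
|---|---|---|---|---|
| 0 | 0.5 | 0.049 | 0.042 | 0.046 |
| 0 | 0.7 | 0.057 | 0.040 | 0.052 |
| 0.28 | 0.5 | 0.457 | 0.461 | 0.565 |
| 0.28 | 0.7 | 0.466 | 0.474 | 0.734 |
| 0.56 | 0.5 | 0.958 | 0.965 | 0.989 |
| 0.56 | 0.7 | 0.958 | 0.969 | 0.999 |

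The rule recovers little of the gain. Its type I error is below 0.05 because it adjusts in just those trials where a chance V0 imbalance would otherwise favour rejection.

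**6. Centre.** If centre carried 5% of the variance (assumed), adding it to V0 at r = 0.5 would move power from 0.559 to 0.580 (d = 0.28) or from 0.988 to 0.991 (d = 0.56).

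**7. Within-subject crossover contrast.** Here the analysed quantity is the difference between a participant's two periods. With r01 and r02 the correlations of V0 with periods 1 and 2, and r12 that between periods, V0 removes a share (r01 - r02)²/[2(1 - r12)] of the variance:

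- (0.5, 0.5, 0.5): 0%;
- (0.6, 0.5, 0.6): 0.01/0.8 = 1.25%;
- (0.7, 0.49, 0.7): 0.0441/0.6 = 7.35%.

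Simulated power in the first case is 0.954 with and without V0. A constant centre effect cancels in the difference.

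**The case against.** The best defence is that the article is condensed and much of the model is unstated. Four stronger readings are tempting, and the document does not support them.

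- **Centre is left out of the analysis.** A reader might infer this from its absence in section 2.13. But the levels of the multilevel model are not named, and a full list of terms is commonly left to an analysis plan. Only this stands: centre is the stratum and is not named.
- **V0 information is thrown away.** Section 2.12 speaks of change from before to after App use, and section 2.13 of putting all measurements in the model, so V0 may already enter as a response or through change. The gain is then 25% to 15% of variance rather than 25% to 49%, and the covariate rule still stands in the text.
- **Power is only 0.45.** That figure requires 0.28 to be a two-sample d, which does not reproduce the stated 172. It raises a question about the sample size, not about covariates. Read as f, the gain is 3 to 4 percentage points at r = 0.5 to 0.7.
- **Adjustment always adds power.** Section 2.12 names both a crossover ANOVA and a between-group post-intervention effect. For a purely within-subject contrast, V0 and centre add almost nothing.

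Nor does the rule raise the false-positive rate; it lowers it slightly. None of these replies defends using a baseline comparison to choose covariates.

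**Conclusion.** The concern holds in a limited form. The covariate rule in section 2.13 makes the primary model depend on chance baseline differences, whichever contrast is primary. The cost in precision depends on the contrast. For the between-group post-intervention effect, fixed V0 adjustment takes power from 0.45 to 0.56-0.72 (d = 0.28) or from 0.955 to 0.988-0.999 (d = 0.56) against an unadjusted end score, with smaller or equal gains against a change score. For the within-subject crossover effect it is near nil. These figures rest on assumed correlations of 0.5 to 0.7, an assumed 0.05 baseline level and 86 evaluable participants per group. Type I error under the rule is about 0.04, on the conservative side. The point on centre is secondary: a term to name, not a proven omission. The change is worth making before analysis, but the flaw does not invalidate the trial.

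**What to change.** Delete the baseline comparison and the covariate rule that follows from it. In their place, state that the model always includes the V0 value of the outcome being analysed and centre as fixed effects, whatever the observed balance. Say once which role V0 takes: a covariate, or a response with a baseline mean common to both groups, but not both. Present baseline characteristics and scores by group descriptively, without tests.

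The cost is a change of wording and about three degrees of freedom (one for V0, two for three centres). No extra participants, visits or data are needed.
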